### 2.3. Project Design and Phases

This project adopts a non-experimental, mixed-methods, multicenter design, with an estimated duration of 12 months. It consists of two interdependent phases:Phase 1—Cross-sectional National Survey: This phase addresses the primary objectives and serves as the foundation for the protocol. A national survey will provide a comprehensive ‘snapshot of how things are at a specific time’ [88]. This approach effectively identifies trends and variations across populations, addressing gaps in existing research [89,90]. The survey will adhere to the STROBE (Strengthening the Reporting of Observational studies in Epidemiology) guidelines to ensure rigor [91].Phase 2—Qualitative Descriptive Study: Building on the survey findings, this phase focuses on the secondary aim. The rationale for conducting a qualitative descriptive study is to ‘provide straightforward descriptions of experience and perceptions’ [92]. This approach is recommended in mixed-methods research to further explore quantitative results [92]. The study will adhere to the COREQ (Consolidated Criteria for Reporting Qualitative Research) guidelines to ensure quality and transparency [93].

### 2.4. Study Population

In Italy, nursing education consists of a three-year university program leading to a bachelor’s degree in Nursing, designed to provide general nursing competencies [94]. This program can offer exposure to mental health knowledge through multidisciplinary courses and internships within National Health Service institutions [95]. However, research indicates that national nursing curricula show considerable variability and lack standardization [96,97], and Italian nurses often graduate with limited psychiatric nursing education [47]. Furthermore, while post-graduate courses in mental health nursing are available, they are not mandatory for employment in psychiatric settings [98]. Based on this context, the study population is defined as follows:Nursing students: Students enrolled in a general nursing program, regardless of year of study, theoretical training, or mental health internship experience.Mental health nurses: Nurses employed in mental health settings, regardless of specialized training in mental health nursing.

### 2.5. Phase 1: Cross-Sectional National Survey

#### 2.5.1. Sample and Sampling Procedure

Given the impracticality and costs of collecting data from the entire target population [89], this study will use convenience and snowball sampling methods [89,99]. These methods ensure efficient recruitment while aiming to achieve a sample representative of the population of interest [89,99]. Participants will be selected based on the following inclusion criteria: (1) consent to participate; (2) proficiency in Italian; (3) students enrolled in a general nursing program; (4) nurses employed in a mental health setting. To ensure consistency and relevance in the responses, the following exclusion criteria will be applied: (1) students who have suspended their program for more than one year; (2) nurses who have suspended work for more than one year; (3) nurses with less than one year of work experience in mental health.

#### 2.5.2. Recruitment Process

Recruitment will initially focus on MHNs employed at the University Hospital and NSs enrolled in the School of Nursing at the primary study center. Recruitment invitations will be distributed via institutional email and local announcements [99]. To ensure national representation, recruitment will extend beyond the primary center. Nursing directors and chief nurses from mental health departments and units across Italian hospitals will be contacted to facilitate survey dissemination among MHNs. Similarly, nursing professors at Italian universities will be contacted to assist in enrolling NSs. Additionally, to align with modern recruitment practices, social media platforms, national mental health nursing associations, and nursing forums will be used to disseminate the survey, engaging MHNs and NSs outside academic or institutional networks.

All potential participants will receive a cover letter explaining the study’s purpose, procedures, and ethical considerations, along with a link to the online questionnaire. Participation will require completing an informed consent form before accessing the survey, ensuring transparency, voluntary participation, and adherence to ethical standards.

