#### 1.4.3. Contextual Factors

Ward characteristics: The wards’ physical environment and operational structure can influence the use of CMs [80]. Working in open versus closed units, or acute versus chronic settings, shapes MHNs’ attitudes toward CMs [64,65,71,77]. Heavy workloads and staffing shortages increase the likelihood of using CMs, as MHNs may lack sufficient resources to manage incidents effectively [79,85]. For instance, shifts with less experienced staff are linked to higher CMs use [64]. Additionally, poor leadership, inadequate safety protocols, and organizational dysfunction contribute to increased reliance on CMs [74,77].

Patient characteristics: Patient-specific factors, such as diagnosis severity and type, are key determinants in decisions to implement CMs [13,85,86]. Patients exhibiting aggressive behaviors or refusing treatment are more likely to experience CMs [14,62,63,65]. Sociodemographic factors also play a role: patient sex [13,71,86,87], age [13], ethnicity [13,87], and marital status [87] can influence CMs use. Additionally, patients admitted involuntarily are more likely to be subjected to CMs compared to voluntary admissions [13].

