#### 2.5.3. Sample Size

According to the Italian Ministry of Health, there are 14,904 MHNs employed in public and private mental health settings across Italy [100]. Additionally, data from the Italian Ministry of University and Research indicate that 55,842 NSs are enrolled in nursing programs nationwide [101,102,103]. Given the lack of prior studies assessing attitudes toward CMs and STs among Italian MHNs and NSs, the prevalence of positive or negative attitudes in these populations is unknown. As a result, the prevalence will be assumed at 50%, which, according to the World Health Organization guidelines [104] and established methodologies for sample size determination in survey research [105], leads to the maximum sample size required.

The required sample size for each population will be determined using Cochran’s formula as outlined by Barlett and colleagues [105]:$$n=\frac{t^{2}*[p*\left(1-p\right)]}{e^{2}}$$
where n = required sample size; t = t-value (1.96 for a 95% confidence interval in populations with more than 120 subjects); p = assumed proportion (0.5 for a prevalence of 50%); and e = acceptable margin of error. This formula has been used in other recent healthcare publications [106].

Using this approach, considering a 95% confidence interval, a 5% margin of error, and a 50% assumed prevalence for maximization, the sample size required is shown below:$$n=\frac{1.96^{2}*[0.5*\left(1-0.5\right)]}{0.05^{2}}\approx 384$$

Thus, to ensure the statistical significance of the results, the survey will include at least 384 participants from each population.

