The questionnaire will be structured as follows:1.Sociodemographic variables: In this six-item section, participants will provide demographic information including sex, age, marital status, ethnicity, and spiritual beliefs. They will also indicate their current role (MHN or NS) to ensure they receive the appropriate subsequent questions. The anticipated completion time is two minutes.2a.Questions for MHNs: In this 14-item section, MHNs only will answer questions about their working role (i.e., clinical or chief nurse), educational level (e.g., bachelor’s or master’s degree), education in mental health nursing (i.e., yes or no), years of work experience, years of work experience in mental health, geographical region, work setting (i.e., acute, community, residential), contract type (i.e., permanent or fixed-term), work schedule (i.e., full-time or part-time), and work pattern (i.e., shift or daytime). They will also assess their perceived workplace safety, job satisfaction, intention to change work settings, and inclination to leave the profession, using a 5-point Likert scale (1 = not at all; 5 = very). The anticipated completion time is five minutes.2b.Questions for NSs: In this nine-item section, NSs only will be asked about the geographical region where their program is located, academic status (i.e., full-time or part-time student), year of enrolment, education in mental health nursing (i.e., yes or no), internship pattern (i.e., shift or daytime), and hours spent in mental health internships. Additionally, they will evaluate their academic satisfaction, intention to leave the program, and interest in working in the mental health field using a 5-point Likert scale (1 = not at all; 5 = very). The anticipated completion time is four minutes.3.Attitudes towards CMs and STs: In this eight-item section, participants will assess the appropriateness of CMs and STs commonly used in psychiatry according to the literature, including physical restraints, pharmacological restraints, locked ward doors, video surveillance systems, body-worn cameras, fixed alarms, portable alarms, and metal detectors. Responses will be collected using a 5-point Likert scale (1 = not at all appropriate; 5 = very appropriate). The anticipated completion time is four minutes.4.Depression Anxiety Stress Scale (DASS-21): This 21-item scale measures levels of depression, anxiety, and stress [115]. Participants will report the frequency of symptoms experienced over the past week on a 4-point Likert scale (0 = never; 3 = almost always). The total score for each dimension will be calculated. Internal consistency values are α = 0.82 for depression; α = 0.74 for anxiety; α = 0.85 for stress. The anticipated completion time is seven minutes.5.Opening Minds Stigma Scale for Healthcare Providers (OMS–HC): This 12-item scale measures stigma towards mental illnesses, focusing on attitudes towards people with mental illnesses and disclosure of mental illness [116]. Participants will indicate their agreement with each statement using a 5-point Likert scale (0 = strongly disagree; 4 = strongly agree). Higher scores indicate greater levels of stigma. Internal consistency values are α = 0.74 for stigma towards people with mental illness and α = 0.86 for stigma towards disclosure. The anticipated completion time is five minutes.6.Healthcare Professional Humanization Scale (HUMAS-I): This 19-item scale evaluates the humanization of care across five dimensions: affection, self-efficacy, emotional understanding, optimistic disposition, and sociability [117]. Participants will rate the frequency of their experiences using a 5-point Likert scale (1 = never; 5 = always). Aggregate scores will be calculated for each dimension and the overall scale. Internal consistency values are as follows: α = 0.87 for affection; α = 0.82 for self-efficacy; α = 0.81 for emotional understanding; α = 0.82 for optimistic disposition; α = 0.70 for sociability. The anticipated completion time is seven minutes.7.Willingness to participate in an interview: A dichotomous question (yes/no) will determine participants’ willingness to engage in the interview.

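### The employer invitation to nurses names only hospital-based contacts, although the target population includes community and residential nurses, so nurse results on coercive measures may tilt toward hospital views

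*Protocol article*

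**What the plan says.** **Population.** Section 2.4 defines the nurse group as "Nurses employed in mental health settings, regardless of specialized training in mental health nursing". Section 2.5.3 counts it: "there are 14,904 MHNs employed in public and private mental health settings across Italy". Neither statement confines the group to hospitals.

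**Recruitment.** Section 2.5.2 begins: "Recruitment will initially focus on MHNs employed at the University Hospital and NSs enrolled in the School of Nursing at the primary study center". It then widens recruitment for the stated purpose of national representation: "Nursing directors and chief nurses from mental health departments and units across Italian hospitals will be contacted to facilitate survey dissemination among MHNs". Beyond these employer contacts, "social media platforms, national mental health nursing associations, and nursing forums will be used to disseminate the survey", with the purpose of "engaging MHNs and NSs outside academic or institutional networks". Section 2.5.1 adds snowball sampling and says the methods aim at a representative sample.

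**Measurement.** Section 2.5.4, item 2a, records each nurse's "work setting (i.e., acute, community, residential"). Of the eight attitude items in part 3, three concern coercive measures (physical restraint, pharmacological restraint, locked doors) and five concern security technologies.

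**Premise.** Section 1.4.3 says that "Working in open versus closed units, or acute versus chronic settings" shapes nurses' attitudes toward coercive measures.

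**Limitations.** Section 2.8 admits that more accessible or more willing people may be over-represented and that geography may be uneven. It does not mention care setting.

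**The concern.** Hospital nurses have an extra way in: their own director or chief nurse passes on the link. No community service or residential facility is named as a contact, so nurses there depend mostly on open channels and on colleagues forwarding the survey. Recruitment route is then linked to care setting, and the article treats a closely related feature of setting as a driver of attitudes to coercive measures.

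Two results are exposed. The first is the description of nurses' attitudes to the three coercive measures (first primary aim). The second is the nurse-student contrast in Hypothesis 1 for the same items. Students are enrolled at universities and are approached through university professors, so their institutional route matches their population. A setting tilt among nurses would therefore pass straight into the difference. Recruiting more nurses by the same routes would narrow the interval without moving its centre.

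**Working it through.** **1. The plan's own figure.** Section 2.5.3 uses t = 1.96, p = 0.5 and e = 0.05:

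n = 1.96² × 0.25 / 0.05² = 384.16, which reproduces 384.

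The stated sample size is not in question. The 5% margin covers random error only.

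**2. Population against route.**

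| Element | Scope in the article |
|---|---|
| Nurse population (2.4, 2.5.3) | all mental health settings, public and private |
| Work-setting item (2.5.4) | acute, community, residential |
| Employer contacts (2.5.2) | University Hospital; departments and units across hospitals |
| Other routes (2.5.1, 2.5.2) | social media, associations, forums, snowballing |

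The article states no quota, target or weight by setting. The questionnaire content it lists has no item on recruitment route.

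**3. Size on the proportion scale.** The documents give neither the hospital share of nurses nor attitudes by setting, so all inputs here are assumptions.

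Bias b = (hospital share in sample − hospital share in population) × (hospital proportion − non-hospital proportion).

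Standard error at p = 0.5, n = 384: √(0.25/384) = 0.0255.

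Coverage of a nominal 95% interval = Φ(1.96 − b/SE) − Φ(−1.96 − b/SE).

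| Over-representation | Attitude difference | Bias | Coverage |
|---|---|---|---|
| 10 points | 5 points | 0.5 points | 94.6% |
| 20 points | 10 points | 2 points | 88% |
| 30 points | 20 points | 6 points | 35% |
| 40 points | 30 points | 12 points | 0.3% |

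**4. Size on the 5-point rating scale.** An SD of 1 is assumed. Half-width = 1.96/√384 = 0.100.

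- Non-hospital nurses 40% of the population, 30% of respondents, ratings 0.3 apart: 0.1 × 0.3 = 0.03; coverage about 91%.
- 50% against 20%, ratings 0.3 apart: 0.3 × 0.3 = 0.09; coverage about 58%.
- 50% against 20%, ratings 0.5 apart: 0.3 × 0.5 = 0.15; coverage about 16%.
- 70% against 10%, ratings 0.5 apart (extreme): 0.6 × 0.5 = 0.30, three times the half-width.

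**5. Cost of standardising afterwards.** Design effect = Σ (population share² / sample share).

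- 50% against 20%: 0.25/0.2 + 0.25/0.8 = 1.56. Width factor √1.56 = 1.25, so the interval is about 25% wider. Keeping the planned margin needs about 384.16 × 1.5625 ≈ 600 nurses.
- 70% against 10%: 0.49/0.1 + 0.09/0.9 = 5.0. Width factor √5.0 = 2.24.

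Reweighting can be expensive if the imbalance is large. Widening the invitation beforehand avoids most of that cost.

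**The case against.** The strongest reply is that the sentence on directors and chief nurses can be read as mental health departments, plus units in hospitals. The article does not say what departments cover, and a full list of services contacted is detail that a condensed article may omit. This stands as a reason for caution. It is also why a clarifying sentence would be an acceptable fix.

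Other parts of the reply also stand:

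- The open routes are expressly meant for people outside institutional networks, and snowballing adds to them. They may offset part of the gap.
- Participation is voluntary on every route and everyone receives the same cover letter and link. Hospital nurses select themselves too; what differs is the employer prompt.
- Section 2.8 already concedes differential accessibility in general terms, and work setting is recorded, so the mix of respondents will be visible.

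Three stronger readings are tempting and lack support. A reader might infer that private-sector nurses are left out, but the hospitals contacted are not limited to public ones. A reader might infer that the tilt is certain, but neither the respondent mix nor the direction of any attitude difference can be derived. A reader might extend the point to security technologies, but the premise in 1.4.3 concerns coercive measures only. It also contrasts open with closed and acute with chronic care, which is close to, but not the same as, hospital against non-hospital.

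What the reply does not remove is the mismatch on a plain reading: the population covers all settings and the named employer contacts are hospital-based.

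**Conclusion.** The point holds as a coverage risk, and it is worth correcting before recruitment. As written, community and residential nurses would be reached mainly through open channels and snowballing. Given the article's own premise about setting, the nurse estimate and the Hypothesis 1 difference for the three coercive-measure items may lean toward hospital views.

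The documents cannot place the study between a negligible bias and one larger than the 5% margin. The range in the working rests wholly on assumed setting shares, assumed attitude differences and, for ratings, an assumed SD of 1. The conclusion also rests on reading the departments contacted as hospital departments. The sample size of 384 is unaffected.

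**What to change.** 1. In 2.5.2, send the same director and chief-nurse invitation to community mental health services and residential facilities. If the departments already contacted include these services, say so.
2. Report nurse attitudes by the work setting that item 2a already collects.
3. Add care-setting imbalance to the limitations in 2.8. If the employer route stays hospital-based, restrict the nurse conclusion to mainly hospital nurses.
4. Optionally, where official counts by setting can be obtained, show a standardised nurse figure beside the raw one as a sensitivity analysis. Its interval may be materially wider, as step 5 of the working shows, so it should not replace the raw figure.

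The cost of the first three changes is more invitation emails, one additional table and a sentence or two of text.

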#### 2.5.3. Sample Size

According to the Italian Ministry of Health, there are 14,904 MHNs employed in public and private mental health settings across Italy [100]. Additionally, data from the Italian Ministry of University and Research indicate that 55,842 NSs are enrolled in nursing programs nationwide [101,102,103]. Given the lack of prior studies assessing attitudes toward CMs and STs among Italian MHNs and NSs, the prevalence of positive or negative attitudes in these populations is unknown. As a result, the prevalence will be assumed at 50%, which, according to the World Health Organization guidelines [104] and established methodologies for sample size determination in survey research [105], leads to the maximum sample size required.

The required sample size for each population will be determined using Cochran’s formula as outlined by Barlett and colleagues [105]:$$n=\frac{t^{2}*[p*\left(1-p\right)]}{e^{2}}$$
where n = required sample size; t = t-value (1.96 for a 95% confidence interval in populations with more than 120 subjects); p = assumed proportion (0.5 for a prevalence of 50%); and e = acceptable margin of error. This formula has been used in other recent healthcare publications [106].

Using this approach, considering a 95% confidence interval, a 5% margin of error, and a 50% assumed prevalence for maximization, the sample size required is shown below:$$n=\frac{1.96^{2}*[0.5*\left(1-0.5\right)]}{0.05^{2}}\approx 384$$

Thus, to ensure the statistical significance of the results, the survey will include at least 384 participants from each population.

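### The 384 per population is a nominal ±5-point precision target for one proportion; it cannot ensure statistical significance and was not sized for the planned tests

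*Protocol article*

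**What the plan says.** Section 2.5.3 starts from the premise that "the prevalence of positive or negative attitudes in these populations is unknown" and therefore plans for one proportion at its least favourable value. The inputs are "t = t-value (1.96 for a 95% confidence interval in populations with more than 120 subjects" and "p = assumed proportion (0.5 for a prevalence of 50", summarised as "considering a 95% confidence interval, a 5% margin of error, and a 50% assumed prevalence for maximization". The section then concludes: "Thus, to ensure the statistical significance of the results, the survey will include at least 384 participants from each population". It mentions neither an effect size nor power.

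Other parts of the Protocol article bear on this conclusion:

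- **Sampling (2.5.1):** "this study will use convenience and snowball sampling methods". Section 2.5.2 adds recruitment through the primary centre, nursing managers, professors, associations and social media.
- **Outcome (2.5.4, questionnaire section 3):** eight items, each rated separately. "Responses will be collected using a 5-point Likert scale (1 = not at all appropriate; 5 = very appropriate". No rating is designated as positive or negative.
- **Hypotheses (2.1):** a nurse–student difference, variation across types of strategy, and associations with sociodemographic and psychological variables.
- **Analysis (2.5.5):** counts and percentages for every variable, then t-tests, one-way ANOVA, Pearson or Spearman correlations, and stratification for confounders, at a 5% significance level.
- **Limitations (2.8):** selection bias and uneven geographical coverage are acknowledged, but not in connection with the 5% margin.

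**The concern.** A margin-of-error formula sets the width of a confidence interval. It says nothing about the probability that a test rejects, and no sample size can guarantee rejection. The closing sentence of section 2.5.3 therefore gives the design a property it does not have, as the stated reason for the sample size of a survey that serves both primary aims.

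Two further mismatches sit behind that sentence. The ±5 points presuppose simple random sampling, which this survey does not use. And the sized quantity is a proportion holding a positive or negative attitude, while the hypotheses are tested on means and correlations and the split itself is left undefined.

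At stake is interpretation. If the sentence stands, a non-significant nurse–student difference or correlation could be read as a negative result from an adequately sized study, and ±5 points could be read as the whole uncertainty of the national estimates.

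**Working it through.** **1. Reproducing the plan's figure.** Inputs from section 2.5.3: t = 1.96, p = 0.5, e = 0.05.

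n = t²p(1−p)/e² = 3.8416 × 0.25 / 0.0025 = 384.16.

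The stated 384 reproduces (strict rounding up would give 385, which is immaterial). Back-calculating, 1.96 × √(0.25/384) = 0.0500, a half-width of 5.0 points. A finite population correction, n/(1 + (n−1)/N), changes little: 374.5 for N = 14,904 nurses and 381.5 for N = 55,842 students.

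The formula contains no difference to detect, no standard deviation and no power.

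**2. What 384 per group gives for the nurse–student comparison.** The document states no effect size and no sidedness. I assume two-sided 5%, the normal approximation, and effects d in standard-deviation units.

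Detectable d at 80% power = (1.960 + 0.842) × √(2/384) = 2.802 × 0.07217 = 0.202. At 90% power it is 0.234.

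Power = Φ(d × √(384/2) − 1.96) = Φ(13.856 d − 1.96):

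| Assumed d | Power |
|---|---|
| 0.10 | 28% |
| 0.15 | 55% |
| 0.20 | 79% |
| 0.25 | 93% |
| 0.30 | 99% |

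Exactly d = 0.20 at 80% power would need 393 per group, so 0.20 is slightly optimistic as a round figure.

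**3. What 384 gives for a correlation within one population** (Fisher z, same alpha).

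Detectable r at 80% power = tanh(2.802/√381) = tanh(0.1435) = 0.143.

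Power = Φ(√381 × atanh(r) − 1.96): 16% at r = 0.05, 50% at r = 0.10, about 78.5% at r = 0.14, 84% at r = 0.15.

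**4. Effect of the planned stratification.** With equal strata, the detectable d within a stratum at 80% power is 2.802 × √(2/n per stratum per group):

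- two strata (192 per group): 0.29
- four strata (96 per group): 0.40

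**5. Multiplicity.** The figures above are unadjusted. As an illustration only, dividing alpha by the eight attitude items raises the detectable d from 0.202 to (2.734 + 0.842) × 0.07217 = 0.258.

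**6. What cannot be computed.** Hypothesis 2 compares items rated by the same respondents, so its power depends on the correlation between items, which the document does not give. Nor does it give anything from which to quantify clustering through units and networks, so I put no number on a widened margin. Selection bias would in any case lie outside such a number.

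**The case against.** The strongest reply is that sizing on a proportion is not foreign to this plan. The first primary aim is descriptive, section 2.5.5 produces percentages for every variable, and the share choosing the upper ratings follows from those by addition. This stands. A reader might infer that the proportion behind the sample size is never analysed; the document does not support that. What remains is narrower: the split is not defined, no interval for it is stated, and no hypothesis test uses it. A condensed article may leave the cut-off and the interval to the full protocol, so their absence alone would not be a point. They matter here because the sample size rests on them.

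Second, section 2.8 already concedes that convenience sampling may bias selection and limit generalisability. This also stands in part: the problem is disclosed, but the 5% margin is never qualified by it.

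Third, the protocol makes no power claim, so the misreading of null results is a risk and not something the plan asserts. That is fair. The sentence nevertheless promises significance outright, and nothing elsewhere in the document corrects it.

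Finally, sample size, recruitment and tests do not change. That limits the cost of the correction, but does not make the sentence true.

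**Conclusion.** The point holds for the stated justification. The claim that 384 per population ensures significance is wrong as written: the calculation delivers a nominal ±5-point margin for one proportion under simple random sampling and nothing about the planned tests. For those tests, 384 per group gives 80% power at about d = 0.202 between populations and about r = 0.143 within one, but only about 28% power at d = 0.10 and 55% at d = 0.15. These figures assume two-sided 5% tests, no multiplicity adjustment, no stratification, independent responses and effect sizes of my choosing.

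A reader might also infer that 384 is too small. The document does not support that: the arithmetic is correct, no target effect is stated against which 384 would fall short, and small-to-moderate effects are detectable before stratification. The fault lies in the justification and its mismatch with the sampling and the tests, not in the number.

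**What to change.** In section 2.5.3:

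1. Delete the significance clause and keep 384 per population.
2. Describe 384 as a nominal ±5-point, 95% precision target for a single proportion that assumes simple random sampling. Note, with a cross-reference to section 2.8, that this margin does not cover selection bias or clustering from the sampling actually used.
3. State what 384 gives for the planned tests at two-sided 5%: 80% power at about d = 0.202 between populations and about r = 0.143 within one, unadjusted for multiplicity and before stratification. Add that the detectable d is about 0.29 with two equal strata and 0.40 with four, and that power is about 28% at d = 0.10 and 55% at d = 0.15, labelled as assumed effects.
4. If the prevalence of positive attitudes remains the sizing quantity, say which ratings count as positive and report that proportion with a 95% confidence interval per item and population, alongside the descriptives already planned. The choice of cut-off belongs to the investigators.

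The cost is a few sentences and, under item 4, one additional table. No extra participants and no change to recruitment or tests are needed; the stated assurance becomes less favourable.
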